#### Secondary outcomes

Key fall-related secondary outcomes will include the number of falls, injurious falls, participants who fall, participants experiencing multiple falls, and time to first fall, as recommended by ProFaNE [57]. The number of falls per physical activity is also assessed to account for risk exposure time for falls [34, 58]. These outcomes will be derived from the same fall reporting strategy described above. Physical activity will be objectively measured over seven days, using a body-fixed sensor (AX6, Axivity Ltd., Newcastle, UK) and validated algorithms [59, 60]. Concerns about falling will be assessed by the Short Falls Efficacy Scale-International, which has been validated in older adults with and without CI [61]. Physical capacity measures will include the Short Physical Performance Battery (SPPB) [62], the TUG [49] and the 2MWT [45, 46], instrumented by inertial measurement units (IMUs; Opal V1, Mobility Lab™, APDM, Inc., Portland, OR, USA) to obtain more detailed movement parameters (e.g., SPPB: postural sway, trunk angle; TUG: sit-to-stand duration, angular velocity of turns; 2MWT: spatio-temporal gait parameters). During the 2MWT, heart rate (Polar Vantage V3, Polar Electro GmbH Deutschland, Büttelborn, Germany) will also be measured to evaluate individual physical effort.

Volitional stepping performance will be assessed with the Choice Stepping Reaction Time Test (CSRT) [63], and the inhibitory CSRT requiring additional response inhibition and response-selection [64].

Static reactive balance will be assessed at FU12 with the modified Stepping Threshold Test (STT) [28, 65], conducted on the BalanceTutor. Single- and multiple-step thresholds - defined as the minimum perturbation magnitudes that trigger one or multiple (≥ 2) recovery steps to regain balance - will be determined based on gradually increasing perturbation intensities. The modified STT used in this study will include an additional initial level with lower intensities to account for more frail individuals. Furthermore, perturbation directions in which a multiple-step threshold is reached remain included in subsequent levels, but at reduced intensity to maintain unpredictability.

Dynamic reactive balance will be assessed at FU12 through observational and kinematic analyses of reactive stepping and laboratory falls in response to eight unannounced submaximal (perturbation intensity level of the BalanceTutor: AP = 15, ML = 10) perturbations (forward, backward, left, right; each during left and right leg swing), applied in random order and at randomized intervals (8–16 s), while walking at an individually preferred speed on the BalanceTutor. This speed will be determined during a 2-min warm-up, following the same procedure as described above for the intervention sessions, but starting at 50% of the overground walking speed measured during the 2MWT at FU12. Additionally, participants will be exposed to one unexpected submaximal forward perturbation (intensity level = 15, swing phase of the left leg) during a 1-min cool-down period, also at the preferred walking speed on the BalanceTutor. The dynamic reactive balance assessment will be video-recorded using a camera (GoPro HERO12 Black, 4 K, 120 Hz, GoPro Inc., San Mateo, California, USA) positioned 59 cm behind the edge of the treadmill platform, perpendicular to the center of the treadmill. The midpoint of the camera lens is set at a height of 103,5 cm from the ground. Data for dynamic reactive balance will be derived from the video recordings, two IMUs (3DT100; MediTouch Ltd., Israel) attached to the participant’s sternum and lumbar region, as well as the center of pressure (COP) data recorded via the BalanceTutor-integrated force plate. Furthermore, participants’ balance recovery strategies in response to the perturbations will be evaluated, applying an adapted version of the Compensatory Arm and Leg Movements (CALM) scale, using video recordings [66]. Video recordings will also be reviewed to determine whether a fall occurred (laboratory fall), defined as a body posture clearly and unambiguously stopped by the BalanceTutor’s safety harness [23].

In the treadmill PBT group, dynamic reactive balance will also be assessed during treadmill PBT sessions three and nine. Participants will receive eight unannounced perturbations (forward, backward, left, right; each during left and right leg swing), applied in random order and at randomized intervals (8–16 s) while walking at the individually preferred speed on the BalanceTutor. The intensity of the AP and ML perturbations will be based on the maximum perturbation intensity achieved during the second treadmill PBT session. Video recordings (CALM, laboratory falls), and IMU and COP data will also be collected during this assessment.

Cognitive functioning will be assessed using the Trail Making Test A and B [67] as well as the MoCA [47].

The 5-level version of the EuroQol-5-Dimension (EQ-5D-5 L) questionnaire and the EuroQol visual analog scale will be used to assess self-reported health-related quality of life and health status [68]).

Acceptability of the treadmill PBT will be assessed in the treadmill PBT group using the Theoretical Framework of Acceptability questionnaire [69].

### Descriptive variables

Age, sex, living conditions, marital status, living situation, and years of education will be collected as sociodemographic information.

Medical information will include comorbidities (Functional Comorbidity Index; [70]), treatments received in the past twelve months, fractures within the past three months, resting blood pressure and heart rate, vibration sensation (Rydel-Seiffer tuning fork), fall risk-increasing drugs, and laboratory parameters (HbA1c, folate, cobalamin), if available from the patient record.

The Mini Nutritional Assessment-Short Form will be used to screen for malnutrition [71].

Frailty status will be assessed using the Clinical Frailty Scale [72]. Self-reported information on the regular use of walking aids in daily life and perceived decline in balance ability over the past 12 months will also be collected.

Intervention fidelity will be measured based on four dimensions [73]: (1) adherence will be quantified based on whether essential components of the intervention session are present or absent, based on a checklist completed by the trainers (i.e., training blocks and perturbations performed, assessment of self-perceived difficulty and anxiety, increase in perturbation intensity, protocol deviations); (2) dosage will be quantified by the number of training sessions completed, and the number and intensity of perturbations received, as automatically recorded by the perturbation treadmill; (3) quality of intervention delivery and (4) participants responsiveness will be measured via a structured questionnaire [69] and focus group interviews of trainers, participants, and health care professionals [74].

### Sample size

The sample size was calculated based on meta-analyses reporting that PBT [75] and gait adaptability training [76], reduce falls by approximately 50% in older adults. For the TRAIL study, it is hypothesized that the intervention group (treadmill PBT) will show a 50% reducion in the incidence of unrecovered falls compared to the control group (CTT). The number of unrecovered falls in the target population is assumed to be 0.5 per person-year [19, 37, 77]. The significance level (α) was set to 5%, and statistical ower at 90%. Sample size calclation was based on a Poisson regression analysis, yielding a required sample size of 132 participants per group to show a significant effect between treatments. The calculation was performed using R 4.0.3 and the WebPower package. Considering an expected dropout rate of 25%, as observed in aprevious intervention study with a similar study population, intervention frequency and duration, and follow-up period [78], sample size increases to 176 participants per group. To account for a potential additional variance due to the multi-center design, the sample size was increased by 10%. Finally, at least 196 participants per treatment group are needed. To obtain equal sample sizes in each group per center, a total of 396 participants (3 × 132 per center) will be recruited.

Losses to follow-up or non-compliance will be included in the intention-to-treat (ITT) analysis.

### Data collection and management

All data will be collected by study nurses and scientific staff. Data will be entered in study-specific electronic case report forms (eCRFs). Furthermore, fall events will be collected using a scannable paper-based fall calendar. Data, registered by the AX6 sensor, the OPAL sensors, the CSRT software, and the Polar watch will be stored on secured servers at each study center. A database constructed using Microsoft Access will be used to extract data in a structured manner, and to organize and standardize the study procedures.

Manuals with standard operating procedures (SOPs) will be used for the conduction of the training intervention as well as the assessments of the study. Prior to the beginning of the study, workshops will ensure standardization, and a similar data quality across all study centers. All study-related measures are documented in these manuals and will be available to all participating partners throughout the study. Data corrections in the eCRF will be documented and are performed by the responsible investigator, or a designated person.

To ensure high quality of data, the completeness, validity and plausibility of data will be checked at the time of data entry (edit-checks), using the database. All data management procedures will be conducted according to written defined SOPs and comply with good clinical practice (GCP). Data will be stored, using pseudonym-codes at the respective study centers first. In frequent intervals Ulm University will collect all data from the study centers, perform plausibility checks, and merge them for statistical analysis.

### Data monitoring and oversight

Risk-based monitoring will be conducted based on the International Council for Harmonization – Good Clinical Practice (ICH-GCP E6) guidelines and SOPs to verify that participants’ rights and wellbeing are protected, reported study data are accurate, complete and verifiable from source documents, and that the study is conducted in compliance with the currently approved protocol/amendment, based on ICH-GCP requirements to ensure safety and integrity of clinical study data. To ensure data accuracy for primary and secondary outcomes, 10% of the source data will undergo verification.

An advisory board consisting of three international experts in the field of PBT in older adults was established to provide scientific oversight, offer feedback, and support the conduct of the study.

### Statistical analysis

The primary outcome, the rate of unrecovered falls within 12 months after the end of the intervention period, will be compared between groups by a multi-level Poisson regression model with study center and randomization block as random effects, at a two-sided significance level of 5%. Analysis of the primary outcome will be done on the full analysis set according to the ITT principle, which will include all randomized participants analyzed in the group they were assigned to. Missing values will be replaced using multiple imputation by chained equations (MICE) with predictive mean matching as imputation method, assuming missing data are missing at random. In total, 10 datasets will be created based on the available data analyzed. Rubin’s rules [79] will be applied to pool results from each dataset. As a sensitivity analysis, a per-protocol analysis will be conducted, consisting of all participants without major protocol violations and with available data on the primary outcome. The intervention effect on secondary outcomes will be analyzed using the same approach as the primary outcome. Additionally, the effect of cognitive status on the primary outcome and key secondary outcomes (total falls, injurious falls, participants who fall, participants experiencing multiple falls, time to first fall, and falls per physical activity, dynamic reactive balance) will be investigated as subgroup analyses. The safety analysis will include calculation of frequencies and rates of (severe) adverse events (AEs) together with 95% confidence intervals on all randomized participants as treated. The analysis will be fully specified in a statistical analysis plan prior to database lock, and will be conducted using R and SAS/STAT^®^ software.

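### The primary Poisson model has no term for differences between participants in fall rate, so its 5% level is exceeded if counts are overdispersed

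*Protocol article*

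**What the plan says.** The Statistical analysis section of the protocol article compares the rate of unrecovered falls over 12 months with a "multi-level Poisson regression model with study center and randomization block as random effects, at a two-sided significance level of 5" percent. It names no negative binomial model, participant-level random effect, scale parameter or robust variance. The one sensitivity analysis is per-protocol, which leaves the distribution untouched. Missing values are to be imputed by chained equations with predictive mean matching in 10 datasets and pooled by Rubin's rules. A later SAP is to specify the analysis fully.

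The Sample size section uses the same distribution. It states that "The number of unrecovered falls in the target population is assumed to be 0.5 per person-year" and that the intervention group "will show a 50% reducion in the incidence of unrecovered falls compared to the control group (CTT"). The calculation "was based on a Poisson regression analysis, yielding a required sample size of 132 participants per group". It then allows for 25% dropout and adds 10% for the multi-centre design.

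The Secondary outcomes section lists "participants experiencing multiple falls" as an outcome in its own right.

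**The concern.** A Poisson model assumes that, given its terms, every participant in an arm has the same fall rate, so that the variance of the counts equals their mean. The article describes a population in which that is unlikely:

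- It pools people with and without cognitive impairment, and clinical with community recruits.
- The Background says that the inability to get up rises with age and is associated with poorer cognition.
- Repeat fallers are expected.

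Any spread in individual rates pushes the variance above the mean.

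The two random effects do not absorb that spread. Randomization is 1:1 in blocks within site, so the arms are contrasted among people who share a block and a centre. Their intercepts remove variation between blocks and between centres. The variation that drives the error of the treatment contrast lies between people in the same block.

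At stake is the primary confirmatory test: a confidence interval that is too narrow, a p-value that is too small, and a nominal 5% error rate that is not the real one.

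**Working it through.** **Inputs from the article.** Control rate 0.5 per person-year; rate ratio 0.5, hence 0.25 in the intervention arm; two-sided 5%; power 90%; 12 months of follow-up; 25% dropout; 396 randomized, or 198 per arm; 10 imputations.

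**Assumptions.** Counts are negative binomial with variance μ + kμ². The article gives no k, so it is varied from 0 (pure Poisson) to 3. Block sizes of 4 or 6 are assumed for the simulation.

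**1. The plan's own sample size.** The Wald formula for the log rate ratio is n = (1.960 + 1.282)² × (1/0.5 + 1/0.25) / (ln 2)² = 131.2, rounded up to 132 per group. This matches the article, and does so with variance equal to the mean. Then 132/0.75 = 176 and 176/0.9 = 195.6, rounded up to 196. No overdispersion allowance enters.

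**2. A single Poisson fit under the null.** With μ = 0.5 in both arms, the true variance is φ = 1 + 0.5k times the Poisson variance. The real type I error is 2[1 − Φ(1.96/√φ)].

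**3. Does the block effect repair this?** Simulation under the null: 3 sites of 132, a Poisson mixed model with a random block intercept, 1,000 runs per k, no centre effect simulated. Rejection rates were identical to those of plain Poisson. At k=1 the mean model SE was 0.143 against an empirical SD of 0.175; at k=2, 0.144 against 0.204. A participant-level robust SE in the same runs rejected in 4.4% to 5.9%.

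**4. With the planned imputation.** Suppose that a fraction f = 0.25 of counts is missing at random and properly imputed within arm, with m = 10. In units of the complete-data Poisson variance:

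- within-imputation variance W = 1
- between-imputation variance B = φ·f/(1−f) = φ/3
- variance that Rubin's rules report: T = 1 + 1.1B
- true variance of the pooled estimate: V = φ/0.75 + B/10
- type I error = 2[1 − Φ(1.96·√(T/V))]

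Example for k=1: φ = 1.5 and B = 0.5, so T = 1.55 and V = 2.05. Then 1.96 × √(1.55/2.05) = 1.704, which gives 8.8%.

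| k | φ | Step 2: single fit, formula | Step 3: single fit, simulated | Step 4: imputed within arm, formula |
|---|---|---|---|---|
| 0 | 1.00 | 5.0% | 4.4% | 5.0% |
| 0.5 | 1.25 | 8.0% | 8.4% | 7.0% |
| 1 | 1.50 | 11.0% | 11.1% | 8.8% |
| 2 | 2.00 | 16.6% | 16.0% | 11.9% |
| 3 | 2.50 | 21.5% | 20.2% | 14.2% |

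Imputation softens the inflation because imputed counts are drawn from observed ones. Part of the overdispersion therefore enters B, although W stays too small. The last column depends on the imputation model, and about 8% at k=0.5 is also a fair reading.

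**5. Power of a correctly dispersed analysis.** At rates 0.5 and 0.25 the variance of the log rate ratio is (6 + 2k)/n. With 198 × 0.75 ≈ 148 completers per group, power = Φ(ln 2/√((6+2k)/148) − 1.96). This gives 93%, 89%, 85%, 76% and 68% for k = 0, 0.5, 1, 2 and 3.

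**The case against.** **The magnitude depends on the whole plan.** Figures of 17% to 22% come from one Poisson fit to complete counts, whereas the plan imputes and pools. This objection stands, and step 4 answers to it. A simulation of predictive mean matching on an uninformative covariate went lower still: 3.4%, 3.6%, 6.7%, 8.3% and 8.5% for k = 0, 0.5, 1, 2 and 3. Part of that drop arises because such matching mixes the arms. With less missing data the results move back towards the single-fit figures.

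**k is not in the article.** This also stands. A reader might try to recover it: 0.5 unrecovered falls per person-year, with half of falls unrecovered, suggests about one fall per person-year, and a faller share of 40% to 50% would then put k at about 1 to 2.4. The article does not support that step. It gives no cohort faller share, the 40% is an individual entry threshold, and the result would describe total falls, not unrecovered ones.

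**The SAP will settle it.** This stands only in part. A robust variance is compatible with the published sentence and could still be added in the SAP. But the distribution and the random effects are already stated, so the point concerns a stated choice and not an omitted detail. An SAP that follows the sentence as written inherits the problem.

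**Conclusion.** The point holds, conditionally. The stated model has no participant-level variance term, and neither centre nor block stands in for one. If k exceeds zero, the model-based SE is too small. At k of 1 to 3 the type I error is about 11% to 22% for a single Poisson fit and roughly 9% to 14% with a quarter of counts imputed within arm. These figures assume negative binomial counts at 0.5 per person-year and data missing at random.

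Four stronger readings are not supported:

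- **The 5% level certainly fails.** At k=0 it holds, and at small k the excess is modest. Overdispersion is likely here, but it is not documented.
- **The plan's error rate is 17% to 22%.** That ignores the planned imputation and takes k at 2 to 3.
- **The block effect or the three-centre random intercept must go.** The block term left rejection rates unchanged, and no effect of the centre term on the primary test has been shown.
- **One Poisson model serves every secondary outcome.** The article says that secondary outcomes follow the same approach, but these include proportions, time to first fall and continuous scores, so it cannot mean that literally. The point carries over to the counts, total falls and injurious falls.

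The 10% multi-centre increase adds participants. It cannot restore the significance level.

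**What to change.** Before database lock, state one of two primary models: a negative binomial regression with a log person-time offset, or the Poisson model with a participant-level robust variance. Apply the same choice to total falls and injurious falls. The centre and block terms may stay, and the rate ratio remains the estimand.

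The edit is about one sentence in the protocol and SAP. The real cost is wider confidence intervals and lower power than the sample size section claims: about 89% at k=0.5 and 85% at k=1 with 148 completers per group, against the stated 90%. The SAP should say openly that this changes the published primary analysis.

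### Fixing 10 imputed datasets for the primary analysis, with 25% dropout planned, leaves avoidable Monte Carlo noise in the primary p-value (minor, free to improve)

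*Protocol article*

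**What the plan says.** The Statistical analysis section of the protocol article describes the primary test as a multi-level Poisson regression of the unrecovered fall rate, "at a two-sided significance level of 5" per cent, on all randomised participants. For missing data it says: "Missing values will be replaced using multiple imputation by chained equations (MICE) with predictive mean matching as imputation method", under a missing-at-random assumption. The number of imputations is then fixed: "In total, 10 datasets will be created based on the available data analyzed". Rubin's rules "will be applied to pool results from each dataset".

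The Sample size section gives the planned extent of missing data ("Considering an expected dropout rate of 25" per cent) and adds: "Losses to follow-up or non-compliance will be included in the intention-to-treat (ITT) analysis". Imputation will therefore carry a real share of the primary analysis. The same section sets the control rate: "The number of unrecovered falls in the target population is assumed to be 0.5 per person-year".

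The article defers full specification of the analysis to a statistical analysis plan, due before database lock. The number 10 is nevertheless already stated.

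**The concern.** Multiple imputation replaces missing values by random draws, so the pooled estimate, its standard error and the p-value depend on the draws made. With few imputations, two correct analyses of the same locked data that differ only in the random seed can give clearly different p-values. The usual defence of a small number is relative efficiency, 1/(1 + FMI/m), which is 0.976 at FMI 0.25 and m = 10. That figure describes the variance of the estimate over repeated trials. It does not say how stable the p-value is for one given dataset.

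The trial has one primary test at 5%. Should the result fall near the threshold, part of the verdict would come from the seed. Such a result is not far-fetched: the trial is powered for a 50% reduction, while the Background and Discussion cite a more recent meta-analysis with 39%, and the Background a non-significant 22% from a trial of treadmill perturbation training against conventional treadmill training.

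**Working it through.** **Inputs from the protocol article.** m = 10; Rubin's rules; two-sided 5%; control rate 0.5 per person-year; planned rate ratio 0.5; 25% dropout; 396 participants, so 198 per group.

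**Assumption.** The FMI is not in the document. The 25% is a planning rate for dropout. Falls are recorded continuously with monthly contact, so a dropout contributes partial follow-up and the FMI may well be below 0.25. I use 0.10 to 0.25.

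**The plan's own figure.** Wald test of the log rate ratio: n = (1.960 + 1.282)² × (1/0.5 + 1/0.25) / (ln 0.5)² = 131.2, so 132 per group, as stated. Then 132/0.75 = 176, and 176/0.9 = 195.6, so 196, also as stated.

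**Noise from the seed.** With the data held fixed, let the total variance with unlimited imputations be 1, made up of within-imputation variance 1 − FMI and between-imputation variance B = FMI. With m imputations:
- the pooled estimate varies over seeds with variance FMI/m;
- B is itself estimated, as B × χ²(m−1)/(m−1);
- the total variance is (1 − FMI) + (1 + 1/m) × estimated B, referred to a t distribution.

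At FMI 0.25 and m = 10 the estimate moves by √(0.25/10) = 0.158 standard errors (one SD) from the seed alone. Adding the noise in the standard error, the SD of the pooled z is 0.20 at m = 10, 0.09 at m = 50 and 0.06 at m = 100.

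**A dataset whose p-value with unlimited imputations is 0.04** (simulated over seeds):

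| FMI | m | central 95% of p |
|---|---|---|
| 0.10 | 10 | about 0.024-0.069 |
| 0.10 | 100 | about 0.034-0.047 |
| 0.25 | 10 | about 0.016-0.103 |
| 0.25 | 100 | about 0.030-0.054 |

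The choice of degrees-of-freedom formula moves these limits by no more than about 0.002. With 10 imputations, about 25% (FMI 0.10) to 40% (FMI 0.25) of seeds lose significance; with 100, about 1% to 9%.

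**Across all trials.** The expected z is |ln RR| / √[(1/0.5 + 1/(0.5 RR)) / (198 (1 − FMI))]. For RR 0.50 this is 3.78 at FMI 0.10 and 3.45 at FMI 0.25; for RR 0.61 it is 2.87 and 2.62. The share of trials in which a run with m imputations contradicts the verdict with unlimited imputations is:

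| true reduction | m = 10 (FMI 0.10 to 0.25) | m = 100 |
|---|---|---|
| 50% (planned) | about 0.7% to 2.5% | about 0.2% to 0.7% |
| 39% | about 2.4% to 5.6% | about 0.7% to 1.6% |

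**Validity and power.** Under the null, the rejection rate at m = 10 is about 4.9%. Under the planned effect at FMI 0.25, power is 92.0% at m = 10 and 93.0% at m = 100; at FMI 0.10 the loss is smaller still. These calculations leave out the centre and block random effects.

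**The case against.** Ten imputations break no rule of valid inference, and the protocol article is not wrong to call the analysis intention-to-treat with Rubin's rules. That stands, and it limits the point to one of precision.

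A reader might infer more, in four ways that the document does not support.
- **That the trial's verdict is likely to be decided by chance.** Among simulated datasets picked because their many-imputation p-value lay between 0.03 and 0.08, with FMI about 0.27, a 10-imputation run gave the opposite verdict in about 27% of runs. That rate is conditional on a borderline result, which is uncommon under the planned effect: about 6% of trials at FMI 0.25. The unconditional rates above are the trial's risk.
- **That 25% dropout means 25% missing information.** The Primary outcome section describes calendars, monthly calls, proactive reports and proxy contact, and the outcome is a rate per person-year. Someone who leaves at month 8 has eight months of data. An FMI of 0.25 is therefore near the upper end.
- **That the absence of a seed or of a Monte Carlo error rule is a fault.** Both are ordinary content of the statistical analysis plan, which is not shown. A fixed seed would make the run repeatable and prevent selection among seeds, but would not reduce the noise.
- **That a larger number removes seed dependence.** It only shrinks it. At FMI 0.25 and a limiting p-value of 0.04, about 9% of seeds still lose significance with 100 imputations.

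**Conclusion.** The point holds as a minor one. The protocol article fixes 10 imputations where more would cost almost nothing, and the p-value of the primary test is noisier as a result. The noise matters only near the threshold, and there it is considerable: two- to threefold or larger swings in p are within the ordinary range over seeds. Over all trials the chance of a changed verdict is a few per cent at most in the two effect scenarios tabulated. There is no bias and no inflation of type I error. The size rests on the assumed FMI of 0.10 to 0.25 and on a Rubin's-rules approximation without random effects. The choice of 100 is an example and not derived from a stated tolerance.

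**What to change.** In the Statistical analysis section, or in the statistical analysis plan before database lock, replace 10 imputed datasets with a larger number, for example 100. This is a free improvement: one number in the text and a few minutes of computing, with no added participants, visits or data. It cuts the seed-to-seed SD of the pooled z to roughly a third (0.20 to 0.06 at FMI 0.25) and recovers up to about 1 point of power.

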### Outcomes

Outcome measures will be assessed before the intervention (pre; at maximum two weeks after the screening), within two weeks after the intervention (post), and six (FU6), and twelve months (FU12) post-intervention. Falls will be recorded continuously throughout the entire study period. An overview of the outcome measures, screening parameters, and descriptive variables across the study timeline is given in Table 2.

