For fall reporting in older adults, prospective daily fall calendars with at least monthly reporting, followed by telephone calls to clarify missing data and gather additional details on falls and injuries, have been recommended [57]. Following the recommendations by Zieschang et al. [34] for fall reporting in older adults with CI, the TRAIL study will use a combined strategy of monthly returned daily fall calendars, regular once-monthly telephone calls, and proxy information to provide additional context or assess the plausibility of participant-reported falls in cases of missing, implausible, or contradictory information. The TRAIL study further extends these sources of information by encouraging participants and proxies to proactively report falls, which may enhance the completeness of fall data and support greater participant engagement in the reporting process.

PBT triggers automatic reflex-like balance responses that help to restore equilibrium without the need for conscious cognitive processing. This feature may be particularly beneficial for individuals with CI. In addition to its promising low volume, treadmill PBT is perceived as effective by both older adults and health care professionals [81, 82]. However, these positive perceptions must still be validated in populations with CI.

Reactive balance assessment will be conducted in both groups only at the 12-month follow-up, based on two considerations. First, such assessment could unintentionally influence reactive balance and fall outcomes in the control group, potentially confounding the effects of the PBT intervention. Second, exposing participants to their limits of reactive balance control already at baseline might cause anxiety about upcoming perturbations during the intervention period, which may lead to early dropouts [28]. However, given a successful randomization of participants, we assume a comparable level of reactive balance control in both groups at baseline. Therefore, if training effects are retained, differences in reactive balance may become evident at the 12-month follow-up.

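### Secondary outcomes that have a pre-intervention value are assigned a model naming no baseline covariate, which costs precision if followed as written

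*Protocol article*

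**What the plan says.** The Statistical analysis section says that the rate of unrecovered falls "will be compared between groups by a multi-level Poisson regression model with study center and randomization block as random effects". The test is two-sided at 5%. The section adds the intention-to-treat set, multiple imputation by chained equations and pooling by Rubin's rules. No baseline covariate is named. For the other outcomes it says: "The intervention effect on secondary outcomes will be analyzed using the same approach as the primary outcome". The same section closes its description with a deferral: "The analysis will be fully specified in a statistical analysis plan prior to database lock".

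The Outcomes section says: "Outcome measures will be assessed before the intervention (pre; at maximum two weeks after the screening), within two weeks after the intervention (post"). Further assessments follow at six and twelve months. The Interventions section confirms this for one measure, since it derives habitual walking speed from the 2MWT at the baseline assessment.

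Reactive balance is different. The Discussion says: "Reactive balance assessment will be conducted in both groups only at the 12-month follow-up". The fall outcomes are event data collected during follow-up and have no pre-assessment value of the same kind.

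**The concern.** The primary model was chosen for a count of events after the intervention, an outcome with no pre-assessment value that could be adjusted for. The article then extends that approach to measures that do have one. For a physical test, a questionnaire or a cognitive score, the participant's own starting value is usually the strongest available predictor of the later value. If it is left out, stable differences between people stay in the residual variance and the confidence interval for the group difference is wider than it need be.

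The Conclusions expect functional improvements alongside fewer falls. Those claims would rest on measures such as the SPPB, TUG and 2MWT. The trial was sized only for unrecovered falls, so precision on these other measures depends largely on how they are analysed.

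**Working it through.** **Inputs from the article.** Two-sided 5% level; 1:1 allocation; 396 participants, so 198 per arm; expected dropout 25%, so 198 × 0.75 = 148.5, taken as 148 per arm. The only power stated is 90%, for the primary outcome.

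**Inputs that must be assumed.** The correlation rho between the pre value and the follow-up value, taken as 0.3, 0.5 and 0.7. The power without adjustment, taken as 80% and, as an alternative, 90%. The article gives neither for any continuous secondary outcome.

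**The plan's own figure first.** Two-group Poisson comparison on the log rate ratio, rates 0.5 and 0.25:

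n per arm = (1.960 + 1.282)² × (1/0.5 + 1/0.25) / (ln 0.5)² = 131.2, so 132.

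132 / 0.75 = 176, and 176 / 0.9 = 195.6, so 196. The stated sample size is reproduced. It says nothing about power for continuous outcomes.

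**Effect of adjusting for the own baseline.** For one follow-up visit and a normal approximation, with effect d in SD units and n per arm:

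power = Φ( d·√(n/2) / √(1 − rho²) − 1.960 )

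With 80% unadjusted power, d·√(n/2) = 1.960 + 0.842 = 2.802:

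- rho 0.3: 2.802 / 0.954 − 1.960 = 0.977, power 83.6% (gain 3.6 points)
- rho 0.5: 2.802 / 0.866 − 1.960 = 1.275, power 89.9% (gain 9.9 points)
- rho 0.7: 2.802 / 0.714 − 1.960 = 1.963, power 97.5% (gain 17.5 points)

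With 90% unadjusted power, d·√(n/2) = 3.242. At rho 0.5, 3.242 / 0.866 − 1.960 = 1.783, power 96.3% (gain 6.3 points). At rho 0.5 the gain is at most 12.4 points, reached when unadjusted power is near 60%. It is under 2 points once unadjusted power is about 98%.

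**The same in effect sizes and numbers.** With 148 per arm, the effect detectable with 80% power is 2.802 × √(2/148) = 0.326 SD without adjustment. It is 0.326 × 0.866 = 0.282 SD at rho 0.5 and 0.326 × 0.714 = 0.233 SD at rho 0.7. For d = 0.30 and 80% power, the number needed falls from 175 to 131 per arm at rho 0.5. The expected 148 per arm lies between the two.

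**The case against.** The strongest reply is that the article is silent rather than wrong. It nowhere says that pre values are excluded, and it leaves full specification to an analysis plan that is not shown. A Poisson rate model cannot be applied unchanged to TUG seconds, a quality-of-life index or time to first fall. The sentence must therefore be adapted by outcome, and may mean only the analysis set, the random effects and the imputation. The dependent variable is not defined either: a model of change, or one treating the pre value as a repeated measurement, would use the baseline.

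Much of this stands. A reader might infer that the plan discards the baseline values, and the text does not support that: it lists a model without a baseline term and does not forbid one. A reader might also infer that every continuous secondary outcome is affected, but reactive balance has no pre value in either group. Table 2, which would confirm the visits for each measure, is not shown, so the list above rests on the general statement in the Outcomes section.

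Two further limits apply. Randomization keeps the unadjusted comparison unbiased. Chance baseline imbalance (standard error √(2/198) = 0.10 SD) is already part of its standard error, so it is not a second harm. The outcomes that the Statistical analysis section lists as key are fall outcomes and dynamic reactive balance, and none of the measures at issue here is among them.

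What does not stand is that this is a mere gap. The article specifies an approach and applies it to these outcomes. Even on the looser reading, the components it names include no own-baseline term. Imputation does not supply one: it fills missing values and leaves the between-person variance of observed outcomes as it is.

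**Conclusion.** The point holds as a matter of precision. Followed literally, the stated approach compares the arms on most non-fall secondary outcomes with wider intervals than the collected data permit. Under the assumed correlations, and from 80% unadjusted power, the forgone power is about 4 points at 0.3, 10 at 0.5 and 17.5 at 0.7; from 90% it is about 6 points at 0.5. These figures are illustrations. Quoting a 10-point loss as a property of this trial would go beyond the documents, since both the correlation and the starting power are assumed. The primary outcome, the secondary fall outcomes and reactive balance are unaffected. The change is worth making because it improves a stated method at almost no cost.

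**What to change.** Amend the sentence in the Statistical analysis section and carry the amendment into the analysis plan before database lock, along these lines:

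*Each secondary outcome with a pre-assessment value will be analysed with a model suited to its distribution. The model will include the participant's own pre value as a covariate, retain the study center and randomization block effects, and account for the correlation of repeated values within a participant across the post, six-month and twelve-month visits. Outcomes without a pre value (the fall outcomes and reactive balance) will be analysed without this covariate.*

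The cost is this short amendment. It needs no new data and no further participants, and any missing pre values can be handled within the multiple imputation already planned. Stating the covariate now also avoids any appearance that it was chosen after the data were seen.
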